**Figure 1. The schedule of enrollment, interventions, and assessments**

## **5. Efficacy and Safety outcomes**

### **5.1 Efficacy outcomes**

#### **5.1.1 Primary Efficacy outcome**

The primary efficacy endpoint will be the change from baseline in average number of migraine days per perimenstrual period over cycles 1-3, assessed using headache diary data.

#### **5.1.2 Secondary Efficacy outcomes**

1. Change from baseline in average number of migraine days per perimenstrual period over cycles 4-6
2. Change from baseline in average number of migraine days per outside perimenstrual period over cycles 1-3 and cycles 4-6
3. Change from baseline in mean migraine hours during perimenstrual period over cycles 1-3 and cycles 4-6
4. Change from baseline in mean migraine hours during outside perimenstrual period over cycles 1-3 and cycles 4-6
5. Change from baseline in mean pain visual analogue scale (VAS) during perimenstrual period over cycles 1-3 and cycles 4-6
6. Change from baseline in mean pain visual analogue scale (VAS) during outside perimenstrual period over cycles 1-3 and cycles 4-6
7. Proportion of participants with at least 50% reduction from baseline in number of migraine days during cycles 1-3 and cycles 4-6
8. Proportion of participants using acute pain medication during cycles 1-3 and cycles 4-6
9. Success rate of blinding at cycle 1.5 and cycle 3

## **6. Statistical Considerations**

### **6.1 Study hypothesis**

The primary study hypothesis is that acupuncture is different from medication in reducing

migraine days in women with menstrually related migraine.

## **6.2 Study Populations**

All patients with randomization will be included in the analysis set regardless of whether they receive any treatment. According to the intention-to-treat principle, all analysis will be based on the randomization set. The intention-to-treat (ITT) set will include all randomized participants who have at least one treatment and one primary outcome measure. The per-protocol (PP) set will include all randomized participants who have no major protocol deviation. The safety set will include all randomized participants who receive at least one session of acupuncture.

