### **7.5 Data Blinding Review and Data Management Report**

When the data checking is finished, a data auditing and blinding review meeting will be hold. On the meeting, the data administrators, statisticians, researchers, clinical inspectors, and other related members would have a discussion on the following items according to the data management report and the data lists:

- Distribution of the participants;
- Protocol deviation;
- Possible outlier;

- Baseline data review;
- Outcomes review;
- AEs review;
- Classifying plan of the statistical analysis population;
- Statistical analysis plan.

Participants will be classified to their suitable statistical analysis sets according to the definition in the protocol. No patient can be excluded from the analysis, unless getting the permission of the meeting participants. All the meeting participants should sign the data locking consent, and the data auditing resolution.

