## **7.6 Database Locking**

The database will be locked if it fulfills all the aspects as followed: All the queries have been solved, and the database has been updated; No query has been found through the data inspection; The medical coding has been completed; The plan of the participants' classification has been approved; The final draft of the SAP has been made, and approved by the project leader.

The statisticians and the data administrators will sign the data locking form, and then the database will be locked. The locked database will be sent to the statisticians for further statistical analysis through the data format of SAS.

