### **8.1 Statistical Analysis**

The primary study hypothesis is that acupuncture is different from medication in decreasing migraine days for women with MRM. The primary outcome is the change from baseline in average number of migraine days per perimenstrual period over cycles 1-3, assessed using headache diary data. The primary analysis will be intention-to-treat with the last observation carried forward (LOCF) method. Migraine days during perimenstrual period will be

summarized in each treatment group and compared using mixed-effect model.

The following secondary outcomes will be analyzed using the mixed-effect model, *t* test, Wilcoxon rank-sum test, Chi-square test or Fisher's exact test, as appropriate and the intent-to-treat principal:

1. Change from baseline in average number of migraine days per perimenstrual period over cycles 4-6
2. Change from baseline in average number of migraine days per outside perimenstrual period over cycles 1-3 and cycles 4-6
3. Change from baseline in mean migraine hours during perimenstrual period over cycles 1-3 and cycles 4-6
4. Change from baseline in mean migraine hours during outside perimenstrual period over cycles 1-3 and cycles 4-6
5. Change from baseline in mean pain VAS during perimenstrual period over cycles 1-3 and cycles 4-6
6. Change from baseline in mean pain VAS during outside perimenstrual period over cycles 1-3 and cycles 4-6
7. Proportion of participants with at least 50% reduction from baseline in number of migraine days during cycles 1-3 and cycles 4-6
8. Proportion of participants using acute pain medication during cycles 1-3 and cycles 4-6
9. Success rate of blinding at cycle 1.5 and cycle 3

A two-side test with  $p < 0.05$  will be considered significant for all analyses.

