## **Missing data**

Efficacy analyses will be conducted in the intention-to treat (ITT) set, which will include all randomized subjects of whom the migraine days are measured in at least on post-baseline 1 cycle.

Missing data will be imputed by the last observation carried forward (LOCF) method (2). In addition, to examine sensitivity of the LOCF method imputed the missing data, we will perform a sensitivity analysis with multiple imputation method under the missing at random (MAR) assumption (3) for the primary outcome with missing data. Multiple imputations use the observed data to fill in the missing values repeatedly to give rise to multiple “pseudo-complete” datasets. We will impute the missing data 100 times using the following one of methods 1) regression imputation, if data sets with monotone missing patterns, or 2) Markov chain Monte Carlo imputation, if data sets with other patterns. For this we will use the SAS procedure Proc MI process. Each method will give rise to 100 different imputed data sets. We will fit our final model described before to each of these imputed datasets and then compute an overall estimate of the intervention effect as an average of the imputation specific estimates. The standard error of the overall intervention effect estimate will be calculated using Rubin’s formula. SAS procedure Proc MIANALYZE will be used to implement these tasks.

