### **Sensitivity Analyses for the Primary Outcome**

For the primary outcome, sensitivity analyses will be performed on the per-protocol (PP) set to assess the robustness of the study conclusion to the choice of analysis population. The PP set is a subset of the ITT, which includes all randomized participants who have no major protocol deviations.

In addition, sensitivity analyses will be performed using multiple imputation method for missing data to assess whether the primary outcome is robust to departure from imputed missing data using LOCF method.

There will be between and within-woman differences in menstrual cycle lengths which

inherently confound the outcomes. To evaluate this potential confounder, we will perform a sensitivity analysis that using menstrual cycle length as a control variable in a mixed-effect model.

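### The SAP states three different rules for who enters the primary analysis, and both sets it labels ITT are modified ITT sets

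*Supplement*

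**What the plan says.** SAP 6.2 opens with "All patients with randomization will be included in the analysis set regardless of whether they receive any treatment". It continues: "According to the intention-to-treat principle, all analysis will be based on the randomization set". The sentence after that reads "The intention-to-treat (ITT) set will include all randomized participants who have at least one treatment and one primary outcome measure".

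SAP 6.3.1, under Missing data, says efficacy analyses use the ITT set, "which will include all randomized subjects of whom the migraine days are measured in at least on post-baseline 1 cycle".

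Other sections use the term without settling it:

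- Protocol 8.1 says "The primary analysis will be intention-to-treat with the last observation carried forward (LOCF) method" and defines no set.
- SAP 6.3.3, the primary analysis, names no set.
- SAP 6.3.2 and 6.3.4 refer to the ITT set or population without saying which.
- The sensitivity analyses in SAP 6.3.3 say "The PP set is a subset of the ITT, which includes all randomized participants who have no major protocol deviations".

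On exclusions, Protocol 7.5 says "No patient can be excluded from the analysis, unless getting the permission of the meeting participants". It also says women are classified by the definition in the protocol, but the protocol text available contains none. Protocol 7.6 makes it a condition of database lock that "The plan of the participants' classification has been approved".

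**The concern.** The population is the denominator of the only primary test, and the plan gives it in three forms that cannot all hold. A statistician programming the analysis would have to choose.

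Two of the three forms admit a woman only if something happens after randomisation: she is treated, or she returns outcome data. If those events are related both to arm and to prognosis, the women left in are no longer a randomised comparison. The plan itself invokes the intention-to-treat principle, which is meant to prevent this.

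The meeting in Protocol 7.5 adds discretion. It takes place once data checking is finished, and its agenda covers outliers, outcomes, the classification plan and the SAP. It may permit exclusions from the analysis with no criteria and no protection for the ITT set.

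**Working it through.** **Membership under each rule.** Rule 1 is the first two sentences of SAP 6.2, rule 2 the third sentence, and rule 3 the Missing data text in 6.3.1.

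| Randomised woman | Rule 1 | Rule 2 | Rule 3 |
|---|---|---|---|
| Treated, at least one post-baseline cycle measured | in | in | in |
| Never treated, cycle 1 diary available | in | out | in |
| Treated, no post-baseline cycle measured | in | out* | out |
| Never treated, no post-baseline cycle measured | in | out | out |

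*If a primary outcome measure means a post-baseline value.

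The rules agree only on the first row. The per-protocol set is defined as a subset of the ITT set, so it inherits the ambiguity.

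**Does the missing-data plan bring the excluded women back?** Not as written. Baseline diaries are completed before randomisation (Protocol 2.4.2.4), so a baseline value should exist for every randomised woman. But the SAP does not say that baseline is carried forward when no post-baseline cycle exists. Nor does it extend the multiple-imputation analysis to women outside the ITT set.

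**Planning figures (Protocol 2.4.1.3).** Means 3.1 (SD 2.7) and 5.2 (SD 4.4), difference 2.1 days over 12 weeks, 5% two-sided, 90% power, 68 per arm, raised to 86 for 20% loss.

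- Root-mean-square SD: √[(2.7² + 4.4²)/2] = √13.325 = 3.65.
- Normal approximation: n = 2 × (1.960 + 1.282)² × 13.325 / 2.1², which rounds up to 64 per arm. The t test gives 65.
- Wilcoxon adjustment: 65 × π/3 = 68.07, which matches 68. The protocol does not say which test was entered.
- Loss: 68/0.8 = 85 per arm, against 86 stated.

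The sample size is therefore reproduced and does not depend on this point.

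**Power.** With SE = √(26.65/n), 2.1/SE is 3.35 at n = 68 and 3.77 at n = 86. Power is 91.8% and 96.5% (Welch t: 91.4% and 96.3%). Power is adequate on any of the sets, so the issue is bias and ambiguity.

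**Size of a possible shift.** Let a fraction e of one arm be excluded, none of the other, and let the excluded women's mean differ from that of the women kept by m days over 12 weeks. The arm mean, and so the treatment difference, moves by e × m. Both inputs are assumptions.

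| e (women out of 86) | m = 0.5 | m = 1.0 | m = 2.1 |
|---|---|---|---|
| 5% (4.3) | 0.025 | 0.05 | 0.105 |
| 10% (8.6) | 0.05 | 0.10 | 0.21 |
| 20% (17.2) | 0.10 | 0.20 | 0.42 |

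As a share of 2.1 days: smallest 0.025/2.1 = 1%, largest 0.42/2.1 = 20%. The largest needs the whole planned 20% loss to fall before any measured cycle, in one arm only.

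**The case against.** **The primary analysis may still be full intention-to-treat.** A reader might infer that it is not. The documents do not support that outright. Rule 1 is tied expressly to the intention-to-treat principle and claims to cover all analysis; if it governs, everyone randomised is included. It is also labelled the analysis or randomisation set, so only two statements carry the ITT label. What stands is that the plan contradicts itself, and that its efficacy-specific sentence describes a modified ITT set.

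**The meeting has safeguards.** A reader might picture a vote to drop women by people who know the allocation. Protocol 7.5 describes a blinding review. The default is no exclusion, an exception needs permission, and all participants sign. Classification is approved before lock, the SAP is finalised before code breaking (Protocol 8.2), and statisticians are blinded. Acupuncturists are not among the blinded roles, but they are not listed as attending either. These safeguards lower the risk of selective exclusion. They do not supply criteria, and they do not keep randomised women in the ITT set.

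**Arm-related early loss is not obvious.** The design is double-dummy with blinded participants, needles of the same type, size and number, and matched tablets. Before a first treatment a woman has had no arm-specific exposure, so the treatment condition is unlikely to remove women by arm. A woman who stops for intolerance after one measured cycle stays in through LOCF. This largely stands: bias is possible but not demonstrated. Some risk remains because sham points differ in location and intolerance can arise within the first cycle.

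**A larger effect could be posited.** Excluding 10% of one arm with a gap of 2 days per cycle would give 0.2/0.7 = 29% of the planned difference expressed per cycle (2.1/3 = 0.7). That is not credible: 2 days exceeds the medication arm's whole planned mean per cycle, 5.2/3 = 1.73.

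**Conclusion.** The contradiction is real and should be resolved before the SAP is final, because it leaves the denominator of the only primary test undefined. Both sets labelled ITT, including the one assigned to efficacy analyses, condition on post-randomisation events and so are modified ITT. Protocol 7.5 adds exclusion by permission without criteria.

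The number of women affected and the size or direction of any bias cannot be known from the documents. The range of 1% to 20% of the planned difference rests on assumed one-sided losses of 5% to 20% and assumed differences of 0.5 to 2.1 days over 12 weeks. The case for change rests on the undefined set, not on proven bias or lost power.

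**What to change.** 1. Use one definition in Protocol 8.1 and SAP 6.2, 6.3.1 (Missing data), 6.3.2, 6.3.3 with its sensitivity analyses, and 6.3.4: the primary set is all randomised women in the arm assigned, whatever treatment or diaries followed. This agrees with the first two sentences of 6.2.
2. State how women with no post-baseline cycle enter the primary analysis. Carrying baseline forward would fit the existing LOCF rule; it sets their change to zero, and the SAP should say so.
3. Extend the existing multiple-imputation sensitivity analysis to these women, with baseline value, arm and centre in the imputation model. The SAP lists no imputation variables at present. Multiple imputation then stays a sensitivity analysis and is not mixed into an LOCF primary analysis.
4. Rename the treated-and-measured set modified ITT and keep it as a sensitivity set.
5. In Protocol 7.5, state that the meeting decides per-protocol membership only and may not remove anyone from the ITT set.

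The cost is wording and a little extra programming, with no new data. The downside is small: a few women contribute only imputed outcomes, which add little information but fix the denominator and make the assumptions visible.

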### **3. Safety Assessment**

All the serious adverse events (SAEs) and adverse events (AEs) will be recorded and measured by both participants themselves and clinicians including neurologists and acupuncturists through the whole trial. In our trial, the SAEs will be defined as events requiring hospitalization, causing disability or impaired ability to work, threatening life or resulting in death. AEs will be categorized as acupuncture related or medication related based on its potential association with acupuncture needling procedure by acupuncturists or medication intake procedure within 24 hours. The acupuncture related AEs defined as follows: broken needle, needle phobia, intense pricking, pricking lasting more than half an hour (no matter how intense it is) after acupuncture, hematoma, dermorrhagia, infection, abscess formation at the needling site, other discomfort induced by acupuncture (such as lassitude, numbness, somnolence, nausea, vomiting, palpitation, dizziness, headache, loss of appetite, insomnia, etc), and aggravation of existing symptoms, etc. Given that acupuncture is a minimally invasive therapy inevitably causing pain, pricking with a spontaneously remission within 30 min after acupuncture will be not regarded as acupuncture related AE. The medication related AEs defined as follows: nausea, palpitations, dyspepsia, upper abdominal pain, heartburn, somnolence, dizziness, and sweating attack, etc. The numbers of participants and events of AEs will be recorded. We will compare the proportion of participants who get treatment-emergent adverse events (TEAEs). Participants who get TEAEs at least once will be counted in for the comparison of the proportion.

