#### **4.1 Treatment of the acupuncture group**

In the acupuncture group, participants will be given true acupuncture plus placebo naproxen (2 tablets each time, once per day, will start three days before each predicted onset of the menstruation and continue during the end of their menstrual cycle for 3 cycles). In the event that menstruation begins later than predicted, no adjustment to the treatment will be made. If the MRM occurs earlier than predicted, participants will be asked to begin taking placebo naproxen immediately and one day earlier in the next cycle in an attempt to provide prophylactic coverage. The timing of treatment will be based on information collected (a headache diary) during the baseline phase and will not account for variability in menstruation and migraine onset during the treatment phase. The placebo naproxen will be identical in taste, smell and appearance as true naproxen sustained release tablets.

Acupuncture will consist of preventive treatment (two sessions each week) and premenstrual conditioning treatment (at least three sessions during 10 days before the predicted onset of each menstruation), deliver for 3 cycles. Each session will last for 30 minutes. The acupuncture points for preventive treatment will include both standard and additional points. The standard points are GV20 (Baihui), GV24 (Shenting), GB13 (Benshen), GB8 (Shuaigu), TE20 (Jiaosun), and GB20 (Fengchi). Additional points will be chosen individually depending on the syndrome differentiation of meridians in the headache region: TE5 (Waiguan) and GB34

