#### **4.2 Treatment of medication group**

In the medication group, participants will be given naproxen sustained release tablets (Diao Group Chengdu Pharmaceutical LTD, Chengdu, China) plus sham acupuncture. Naproxen sustained release tablets will be taken with a peri-menstrual dosing strategy (250mg/tablet, 2 tablets each time, once per day), which will start three days before each predicted onset of the menstruation and continue until the end of their menstrual cycle for 3 cycles. In the event that menstruation begins later than predicted, no adjustment to the treatment will be made. If the MRM occurs earlier than predicted, participants will be asked to begin taking naproxen immediately and one day earlier in the next cycle in an attempt to provide prophylactic coverage. The timing of treatment will be based on information collected (a headache diary) during the baseline phase and will not account for variability in menstruation and migraine onset during the treatment phase.

The method of applying blunt needles on effective acupuncture points will be not used in this trial as control for following reason: patients in China are very familiar with the sensations caused by acupuncture and therefore they may easily identify the blunt needles.

To make the needling stimulation consistent, the same type, size, and number of needles will be used for both groups. In order to avoid possible therapeutic effects of sham acupuncture,

the non-effective acupoints are chosen by the following three rules: (1) Acupuncture points that are defined as unrelated to headache or menstruation based on a vast amount of Chinese medicine reference books (26 ancient Chinese books of acupuncture, three Chinese acupuncture textbooks and >100 acupuncture research literatures); (2) 15 acupuncture points in the vicinity of elbow and knee joints are selected while the acupuncture points on the head, hands, feet, and trunk are excluded; (3) To mimic the nature of selecting points based on syndrome differentiation, the 15 sham points in the vicinity of elbow and knee joints are further randomly assigned to 3 subgroups: B, C, D. Each subgroup will have two points on the arms and three points on the legs. The participants in the medication group will be further randomly assigned into one of these three subgroups via central randomization system. Participants will be treated individually to avoid communication on the treatments they received.

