#### **6.3.5 Safety Analyses**

##### **Adverse events**

All adverse events and serious adverse events will be listed. Adverse events include the acupuncture-related adverse events and medication-related adverse events. Chi-square test or Fisher's exact test will be used to compare the incidence of adverse events between the acupuncture group and medication groups.

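### The SAP's safety set is keyed to needling alone, so a woman who took tablets but attended no session is left out, and the SAP's adverse event section neither names a set nor matches the protocol's comparison

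*Supplement*

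**What the plan says.** **The set.** SAP 6.2 reads: "The safety set will include all randomized participants who receive at least one session of acupuncture". Tablets are not mentioned, and sham sessions are neither included nor excluded by name. Earlier in the same section the SAP says that "all analysis will be based on the randomization set".

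**The treatments.** Under protocol 4.1 and 4.2 one arm gets true acupuncture with placebo naproxen and the other gets naproxen with sham acupuncture. On the needling, protocol 4.2 says: "To make the needling stimulation consistent, the same type, size, and number of needles will be used for both groups".

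**The adverse event analysis.** SAP 6.3.5 says that all adverse events and serious adverse events are listed, adds "Adverse events include the acupuncture-related adverse events and medication-related adverse events", and then plans a chi-square or Fisher test of incidence between the groups. It names no analysis set. Protocol section 3 has all events recorded for the whole trial by participants, neurologists and acupuncturists. It sorts them by their link to "acupuncture needling procedure by acupuncturists or medication intake procedure within 24 hours". Its comparison carries no restriction by cause: "We will compare the proportion of participants who get treatment-emergent adverse events (TEAEs"), each woman counted once. It does not define treatment-emergent, and the SAP does not use the term.

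**The concern.** A safety set should hold everyone who was exposed to a study treatment. Here there are two exposures in each arm, and the definition looks at only one of them. The omitted exposure is the tablet, which in the medication arm is the active comparator. Any woman lost to the set through this rule is one who was exposed.

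The second issue is that the SAP does not settle who is counted and what is counted. At least two denominators are open, the randomised set and the safety set. The SAP's sentence on scope names two attributed classes, while the protocol compares treatment-emergent events of any cause. SAP 3.1 gives demonstrating safety as one purpose of the trial, so both the numerator and the denominator of that comparison should be fixed before the data are seen.

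**Working it through.** The plan states no adverse event rate and no power for safety, so there is no safety figure to reproduce. The only design figure used below is the arm size in protocol 2.4.1.3: 68 evaluable women and 20% loss give 68 / (1 − 0.20) = 85 per arm, against 86 stated. The point does not depend on that difference.

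**Step 1: who is outside the set.** Set the rule beside the exposures, taking sham sessions to count as acupuncture:

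| Exposure | In the safety set under SAP 6.2? |
|---|---|
| At least one session and at least one tablet | Yes |
| At least one session, no tablet | Yes |
| No session, at least one tablet | No |
| Neither | No (correct) |

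Only the third row is wrong.

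**Step 2: how many women could be in that row.** Protocol 4.1 schedules two preventive sessions a week and "at least three sessions during 10 days before the predicted onset of each menstruation". Under protocol 4.2 naproxen is taken on a plan "which will start three days before each predicted onset of the menstruation". Day 10 before to day 3 before leaves 10 − 3 = 7 days, about two sessions at two a week, ahead of the first planned tablet. If sham sessions follow the same timetable, most women would have been needled before taking a tablet. That timetable is written only for the acupuncture group; protocol 4.2 matches the needles but gives no sham session schedule. Both arms also start tablets early if a migraine comes early. So the row is probably small, but the documents do not show that it is empty.

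**Step 3: what a small loss does to a rate (illustrative).** Assume 13 of 86 women in the medication arm have an event: 13/86 = 15.1%. Let k tablet-only women be dropped.

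| k | Share of arm, k/86 | Rate if all k had an event, (13 − k)/(86 − k) | Rate if none had, 13/(86 − k) |
|---|---|---|---|
| 1 | 1.2% | 12/85 = 14.1% | 13/85 = 15.3% |
| 2 | 2.3% | 11/84 = 13.1% | 13/84 = 15.5% |
| 4 | 4.7% | 9/82 = 11.0% | 13/82 = 15.9% |
| 8 | 9.3% | 5/78 = 6.4% | 13/78 = 16.7% |

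The shift is minor for one or two women. It becomes material only if several are lost and those women are the ones with events. That could happen if an early reaction to the tablets is why they never attended.

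**Step 4: what is counted.** The SAP lists all events, says that they include the two attributed classes, and tests the incidence of adverse events. The protocol tests treatment-emergent events of any cause. The two agree if the SAP's sentence is an illustration and differ if it is a limit. Attribution is not clear-cut: nausea, palpitation, somnolence and dizziness appear on both symptom lists in protocol section 3, and make up four of the eight named medication-related symptoms.

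**The case against.** The case for leaving the text alone is that both arms are needled, needling would normally come first, and the sentence basing all analysis on the randomised set would lose nobody. The first two parts stand as reasons why the loss is probably small. The third does not settle the matter, because the same section goes on to define a separate safety set and SAP 6.3.5 chooses neither.

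Three stronger readings are tempting, and the documents do not support them.

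- **That the set holds one arm only.** A reader might take acupuncture to mean true acupuncture, which would put all 86 medication-arm women out of 172 outside the set. Protocol section 4 does name acupuncture and sham acupuncture as separate things. But SAP 6.3.5 tests incidence between the two groups, which a one-arm set could not support, and protocol 2.4.1.2 treats sham as one of the acupuncture methods a woman may receive. The wording should be clearer, but a one-arm set is not a credible reading.
- **That delayed or unattributed events are dropped.** Protocol section 3 records all events throughout the trial and compares treatment-emergent events without regard to cause. The 24-hour phrase governs how events are categorised. SAP 6.3.5 lists all events, and its verb does not say only. What remains is a mismatch of wording between the two documents.
- **That unblinded acupuncturists decide the safety result, so a blinded neurologist is needed.** The acupuncturists obtain the allocation and deliver both kinds of needling, and they are not among the blinded roles. But protocol 2.4.2.4 has neurologists assess safety too, and a comparison of all events does not turn on attribution. Nor would blinding be free: neurologists' blinding is not stated, and needle-site events can reveal the arm, because true points include head and abdomen while sham points lie near elbows and knees.

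**Conclusion.** The point holds at minor to moderate severity. SAP 6.2 states a rule that excludes women exposed to tablets but never needled, and it leaves the status of sham sessions unsaid. SAP 6.3.5 names no set for adverse events and is not aligned with the comparison in protocol section 3.

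The expected effect is small. That judgement assumes that sham sessions count and that they follow the timetable written for true sessions; the first is well supported by the text and the second is not stated. The rates in the working are assumed, since the documents give none. The scope problem is an ambiguity and not a stated exclusion of any event. The primary efficacy analysis is untouched.

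**What to change.** 1. In SAP 6.2, define the safety set as all randomised women who received at least one session of true or sham acupuncture or at least one tablet of naproxen or placebo, analysed by treatment received. Make clear that the sentence on the randomised set does not govern safety.
2. In SAP 6.3.5, name that set as the denominator for adverse events.
3. In SAP 6.3.5, state that the between-group comparison covers all treatment-emergent and serious adverse events regardless of attributed cause, with relatedness as a secondary tabulation. Define treatment-emergent once and use the same definition in protocol section 3.

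The cost is a few sentences. No additional data items or staff should be needed: events are already recorded throughout the trial, women already note their acupuncture dates in the diary (protocol 2.4.4.1), and compliance with both needling and tablets is already to be analysed (SAP 6.3.5). The change has to be made before lock, because protocol 7.6 requires the classification of participants to be approved by then.
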